### Data collection by research team

A representative from the research team will review participants in the trial whilst the participant is in ICU throughout the period they are being proned, or the first working day afterwards if this has occurred over the weekend; once they have regained capacity; and at 3 months post discharge. They will collect patient data as detailed in Tables 4, 5 and 6 including standardised risk scoring measures used in ICU with potential relevance to our study (Waterlow, SOFA scores) [8, 9]. Data on device metrics will be obtained through discussion with clinical staff caring for the proned patient. They will ensure complete data sets are recorded through access to the clinical data entry form and spreadsheet, collect personal and nominated consultee opinions as required, and obtain patient consent. Patient notes will not be accessed by members of staff outside of those in the direct team until consent has been obtained.

**Table 4 Tab4:** Data to be collected by local research team—demographics

Patient metrics: Age, height, weight Frailty score Sequential Organ Failure Assessment (SOFA) [9] score on day 1 of proning Waterlow Pressure Ulcer Risk Assessment Scale on day 1 of proning [8] Pre-existing complications before day 1 of proning—see Table 6 ICU pressure sore risk score Medical comorbidities Diagnosis Device metrics—see Table 5 Proning complications—see Table 6

**Table 5 Tab5:** Data to be collected by local research team—device metrics (where clinical team who have used device are available)

Ease of introduction under the patient Ease of inflation/deflation Suitability of speed of inflation/deflation Ease of repositioning—head/arms Manual handling issue/concern Other comments

**Table 6 Tab6:** Data to be collected by local research team—proning complications

Pressure sore (face/chest/pelvis/knees/feet) Nerve injury (neck/arm/abdomen/leg) Blood vessel injury Skin abrasion Organ injury (liver/pancreas/genitals/ocular) Other	

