## Study design, aims, and objectives

### Aim

To determine the change in total staff time required for repositioning proned patients using the BathMat and to assess the safety of use when compared with standard care.

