#### Sample size

A sample size of 30 patients was determined from statistical analysis of the proposed trial. This is sufficient to detect a decrease in repositioning time of at least 10 min with a power of over 95%. An estimated 10-min improvement was identified via a preliminary unpublished volunteer study. This was determined to be the optimal route to estimate the approximate magnitude of time saving before the device was trialled on patients as part of the proposed clinical study.

Power calculations were carried out using Monte Carlo sampling to allow for variability in the number of repositionings per proned session and the number of proned sessions per patient. In addition to standard deviation assumptions, 2–4 repositionings per proning session were used (randomly sampled with proportions (1/5, 3/10, 1/2)) and a dropout rate of 1/3 after the first session. The repeated measurements for each patient were simulated using a correlation of 0.7 within the same treatment and 0.3 between the two treatments.

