## Study procedures

Patients ventilated and identified as suitable for proning by the ICU consultant/senior doctor will be randomised to be repositioned whilst in the prone position with either standard care or the BathMat on a 1:1 basis. The same repositioning method will be used throughout each proning session but will alternate on subsequent proning sessions between BathMat and standard care, if proned more than once. This will account for patient-to-patient heterogeneity in individual variables such as the requirement for PPE and body mass index. A total of 30 participants will be recruited, and each participant will be involved in the study. The SPIRIT figure for the trial is shown in Fig. 6.

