### Safety

Adverse event (AE) reporting will follow Health Research Authority guidance on safety reporting/Medical Devices (MEDDEV) guidance (https://ec.europa.eu/docsroom/documents/16477/attachments/1/translations).

Severity and causality of each with use of the device as per the above guidance. Adverse events and device deficiencies will be recorded by the research or clinical team and reported directly to the site principal investigator using the adverse event reporting form available here as a supplementary document at the above link and available here: https://ec.europa.eu/docsroom/documents/16477/attachments/2/translations. AEs identified in Tables 3 and 5 will be recorded daily by the research team whilst the participant remains within the trial.

An event assessed as ‘severe’ or ‘life-threatening’ will be considered a serious adverse event (SAE) in this trial. Considering that all eligible patients are critically ill and at increased risk of experiencing multiple AEs due to the complexity and severity of their condition, unexpected adverse events are only recorded if they meet the criteria for an SAE and are considered to have occurred as a consequence of the trial itself (i.e. deemed to be ‘possibly’, ‘probably’, or ‘definitely’ related to the trial procedures). Any SAEs, or device deficiencies that would have led to an SAE had suitable action not been taken, intervention not been made, or circumstances been less fortunate, will be reported by the sponsor of the clinical investigation to the UK National Competent Authority, using the standard MEDDEV SAE reporting form and summary tabulation immediately, or at most within the timelines laid out in the above guidance.

Staff members involved in the care of patients enrolled in the study will have the ability to report any concerns regarding adverse device effects and device deficiencies locally to the CI or directly to the central trial group via email contacts displayed at each trial centre.

Any concerns raised by trial teams at each centre, or the Trial Management Group, may result in a pause in the trial data collection pending formal review. This could include the formation of a formal Data Monitoring Ethics Committee.

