### Statistical analysis

We will test for a treatment effect using a linear mixed effects model with repositioning time as the response, fixed effects for site, sequence group assignment, and repositioning method, with random effects for individual to account for repeated measures. Analysis of the number of staff needed to carry out the repositioning procedures will take a similar approach, using a mixed effects cumulative logistic model to account for the discrete nature of the data. All tests will use the conventional 5% significance level.

No imputation or other statistical adjustments for missing data will be undertaken for these analyses. All recorded measurements of repositioning time and the number of staff needed within each proning session for the analysis, which means there is a very low chance that patients will be excluded from the analysis based on missing data. It will not be possible to tell if data on a repositioning exercise is fully missing. Whilst estimates of the treatment effect stratified by case complexity and BMI would be of interest, no sub-group analyses are planned as these would not be statistically reliable given the size of the trial.

This trial is focused on establishing efficacy in relation to the core repositioning outcome. Demonstrating efficacy is a necessary step before progressing to a larger trial that could robustly assess clinical outcomes, such as the prevention of pressure ulcers, which are relatively rare and require significantly larger sample sizes to detect with confidence. As such, this study is not powered to detect statistically significant effects in secondary outcomes, and formal hypothesis testing for these could be misleading. However, collecting and reporting detailed summary statistics will allow assessment of trends, variability, and effect sizes, which are essential for designing an appropriately powered future trial.

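### The daily adverse-event rule cites the wrong table and so omits the Table 6 proning complications; in patients who receive both methods, a complication first found after a switch cannot reliably be assigned to either

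*Protocol article*

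**What the plan says.** The Aim section pairs staff time with a comparative safety aim: "to assess the safety of use when compared with standard care". Under Study procedures, the repositioning method "will alternate on subsequent proning sessions between BathMat and standard care, if proned more than once". The section on the decision to prone expects one session per day.

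Complications are collected by two routes.

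- **Table 3** (tube, line and airway events) is entered on the bedside form after each manoeuvre, so each event is tied to a method.
- **Table 6** is collected by the local research team. It begins "Pressure sore (face/chest/pelvis/knees/feet" and continues with nerve, vessel, skin and organ injury. Table 4 asks for pre-existing Table 6 complications once, before day 1 of proning.

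The research team reviews patients through the proning period, with weekend reviews deferred to the next working day. It reviews them again when capacity returns and at 3 months after discharge (Data collection by research team).

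The Safety section then states "AEs identified in Tables 3 and 5 will be recorded daily by the research team" while the participant remains in the trial. Table 5 is the list of device metrics, such as ease of placement and speed of inflation.

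Table 1 makes adverse incidents secondary outcome b, with a research team form as one source. The 3-month cost of those incidents is outcome d. Both are to be summarised without formal testing.

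**The concern.** Pressure sores and nerve injuries can build up over sessions or be noticed after the session that caused them. In an alternating design the patient may by then have had the other method. To place such an event, the analyst needs to know when it was first seen and whether it was already there before the session began. The rule that would supply this daily names a table with no patient complications in it. The only stated baseline precedes the first session, and no rule says how an event in a patient exposed to both methods is to be counted.

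What is at stake is the comparative safety description and the costs attached to it. The Statistical analysis section says these summaries will serve the design of a larger trial and gives pressure ulcers as an example of what that trial would assess. If events from both methods are mixed, the apparent difference shrinks towards zero, and a future trial would be planned on it.

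**Working it through.** **The plan's own figure.** The protocol gives no rate or power for late complications. Its one power statement ("a decrease in repositioning time of at least 10 min with a power of over 95" per cent) concerns repositioning time. It cannot be confirmed, because the standard deviation is not given. With the stated correlations and session pattern, and a two-sided 5% test assumed, a standard deviation of 12 min gives 97.2% and 13 min gives 94.9%. Nothing below depends on it.

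**Inputs from the Sample size and Blinding and randomisation sections.** There are 30 patients ("A sample size of 30 patients was determined from statistical analysis of the proposed trial"), allocated 1:1, with one third lost after the first session.

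**Assumed inputs.** The document gives no event rates. Let pS and pB be the per-session risks under standard care and BathMat, independent between sessions. I take pS as 5% to 10% and pB as 10% to 30%, for illustration only.

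**Step 1: who receives both methods.** 30 × 2/3 = 20 receive both; 30 × 1/3 = 10 receive one.

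**Step 2: the table references.**

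| Table | Content | Named in the daily rule |
|---|---|---|
| 3 | Immediate repositioning complications | Yes |
| 5 | Device metrics | Yes |
| 6 | Proning complications | No |

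**Step 3: the review schedule against the alternation.** With one session a day, a patient proned on Saturday and Sunday receives both methods before the deferred research review. Reviews on regaining capacity and at 3 months come later still.

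**Step 4: untimed events compared by sequence, at most two sessions.** A two-session patient has risk 1 − (1 − pB)(1 − pS) in either order, so this term cancels:

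- BathMat first: (1/3)pB + (2/3)[1 − (1 − pB)(1 − pS)]
- Standard care first: (1/3)pS + (2/3)[1 − (1 − pB)(1 − pS)]
- Difference: (1/3)(pB − pS), whatever the risks

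For 5% and 15%: 1 − 0.85 × 0.95 = 0.1925, and 2/3 of that is 0.1283. BathMat first is 0.0500 + 0.1283 = 17.8%. Standard care first is 0.0167 + 0.1283 = 14.5%. A 10-point difference appears as 3.3 points.

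| pS, pB | True difference | Standard care first | BathMat first | Apparent difference |
|---|---|---|---|---|
| 5%, 10% | 5 points | 11.3% | 13.0% | 1.7 points |
| 5%, 15% | 10 points | 14.5% | 17.8% | 3.3 points |
| 10%, 20% | 10 points | 22.0% | 25.3% | 3.3 points |
| 10%, 30% | 20 points | 28.0% | 34.7% | 6.7 points |

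**Step 5: other patterns.** If the one-third loss repeats after every session, to a maximum of five, 50% to 60% of the per-session difference remains. If each patient is instead counted under every method received (two sessions at most), each method has 5 single-method and 20 shared patients. At 5% and 15% this gives (5 × 0.15 + 20 × 0.1925)/25 = 18.4% against (5 × 0.05 + 20 × 0.1925)/25 = 16.4%. One fifth of the difference remains.

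**Step 6: what stays assignable.** Events in the roughly 10 single-session patients, and events seen before session 2 in anyone, can be set against the first-session method. At 5% and 15% in 15 patients per group, the expected counts are 15 × 0.05 = 0.75 and 15 × 0.15 = 2.25.

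**The case against.** The strongest reply is that this is a condensed article. Table 6 lists domains and is not a case report form, so a date or session field may exist on the forms. Review during proning with one session a day would date many events. Table 5 in the Safety section is probably a slip for Table 6, and if so daily recording was always intended. Severity and device causality are to be assessed for each event. Table 3 events are already tied to a method. The protocol also says that it is not powered for secondary outcomes.

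Much of this stands, and it rules out stronger readings that a reader might infer.

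- **That Table 6 events are undated, or cannot be assigned at all.** The article does not say the first. The second fails for single-session patients and for events seen before session 2.
- **That each event will be charged to the method in force when it is noticed.** If a share f were exchanged each way, the observed difference would be (1 − 2f) of the true one, vanishing at f = 0.5. No such rule is in the protocol. With 30 first and 20 second sessions and similar risks, only 20 of 50 sessions are followed by a switch, so f cannot exceed about 0.4.
- **That the trial would conceal a harm from the device.** The documents show a loss of contrast in a descriptive summary, no more.

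What the reply does not remove is the wrong reference in an operative safety rule, the single stated baseline and the weekend gap. Correcting the reference would date detection, but would not settle which session caused a lesion that surfaces later. Causality judged by staff who know the method is an opinion on one event, not a comparison of methods.

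**Conclusion.** The point holds in limited form. As written, the daily recording rule misses the proning complications. For about 20 of 30 patients, a Table 6 event first found after a switch cannot reliably be given to one method. Comparing untimed events by sequence would leave one third of the per-session difference with two sessions, or 50% to 60% with up to five. These sizes rest on the protocol's one-third loss after session 1, on independent session risks and, for the worked percentages, on assumed event rates. The primary outcome and its power are untouched. It is worth correcting because comparative safety is a stated aim and the change is small.

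**What to change.** 1. In the Safety section, change the daily recording rule to refer to Tables 3 and 6.
2. Within the existing reviews, record each Table 6 item with the date first seen, the session number and its status before the next session starts.
3. Make the main between-method summary of Table 6 events those seen up to the start of session 2, by randomised first-session method. This is descriptive only, with all 30 randomised patients as the intended denominator, about 15 per group.
4. Report later events by sequence, and state that they are not attributable to one method.

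The cost is a few form fields and an entry before each new session. Treatment, sample size and primary analysis do not change.

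The first-session comparison has limits that should be stated with it. Few events are expected. Lesions that surface after session 2 begins are still missed. Some patients may have had one standard-care repositioning before recruitment. The data rules elsewhere would also reduce the 30: for patients who die (Source data and documents), and for those who decline consent (Refusal or withdrawal of consent), only primary-outcome data are kept. The report should give the number actually contributing in each group.

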### End of study

Participants end their involvement with the study when they no longer require proning and the study has a complete dataset.

### Consent

Patients become eligible for this trial during a period of critical illness. Proning is indicated in patients with moderate to severe lung injury and hypoxaemia. Prior to proning being considered, patients will have been sedated and ventilated as a life-saving measure during an emergency clinical situation. It necessitates the use of sedative and analgesic drugs (as part of standard care), leading to patients lacking mental capacity and/or the ability to communicate effectively. Moreover, the emergency clinical situation can cause profound distress for relatives, raising ethical concerns both about the burden of trying to understand the trial and the ability of a personal consultee (i.e. relative or close friend) to provide an opinion about trial participation during a time of great distress. For these reasons, attempts to obtain either prior informed consent from the patient or the prior opinion of a personal consultee are inappropriate.

We will adopt a Research Without Prior Consent (RWPC) model (also referred to as ‘deferred consent’), whereby eligible patients will be randomised to receive the assigned treatment. This is an accepted consent model in adult emergency and critical care research where participants lack mental capacity, and minimises the distress and additional burden on families during a distressing time. In addition, the urgent nature of treatments delivered in ICU means that any delay to commencing treatment could be detrimental to the patient (and to the scientific validity of the trial). This consent model is covered by an Emergency Waiver of Consent under the Mental Capacity Act (Research Ethics Committee (REC) review approved).

#### Patient informed deferred consent

Following randomisation, patients will be informed of their involvement in a research study once they are deemed to have regained capacity. A delegated member of the site research team will then approach them to obtain informed deferred consent. It is anticipated that this first approach will occur within 24–48 h of regaining capacity but should be performed as soon as appropriate: this may be prior to recruitment in some circumstances. Verbal consent for this discussion will be obtained by a member of the direct clinical team prior to this approach. A participant information sheet (PIS) will be given to the patient. The PIS will provide information about the background/rationale for the trial, what participation means for the patient (e.g. data collection, follow-up questionnaires), confidentiality and data protection, and the future availability of the trial results. Patients will be given time to read the PIS and have an opportunity to ask any questions they may have about participation in our study.

A consent form will be provided indicating that: the information given, orally and in writing, has been read and understood; participation is voluntary and can be withdrawn at any time without consequence. The consent form will also cover consent for access to medical records for ongoing data collection and follow-up.

After verifying that the PIS and consent form are understood, the person seeking consent will invite the patient to sign the consent form and will then add their own name and countersign it. A copy will be given to the patient, a copy placed in the patient’s medical notes, and the original kept in the Investigator Site File. If the patient is unable to physically sign the consent form (e.g. due to weakness, reduced dexterity), an independent witness (i.e. someone not involved in the trial) can sign on their behalf.

In the situation where a patient is approached in hospital but wishes to have more time to consider participation, they can request to be approached via the method detailed in 5.12.4.

#### Personal consultee opinion

It will usually not be possible to involve trial participants in the consenting process early on. Instead, consent will be obtained from patients once they have stabilised and are deemed to have capacity.

In the interim, once notified of the enrolment of a patient into our study, a delegated member of the site research team will approach the personal consultee (in person or via telephone) as soon as appropriate and practically possible to discuss the trial and seek their opinion as to the patient’s likely wishes and feelings regarding participating in the trial. This approach would take place as soon as reasonably possible, ideally within 24–48 h of randomisation, but could be most appropriate once the patient’s medical situation is no longer an emergency.

Where approached in person, the personal consultee will be provided with a personal consultee information sheet, containing all the information provided on the PIS, supplemented with information on why the personal consultee has been approached at this stage. Personal consultees will be given time to read the personal consultee information sheet and have an opportunity to ask any questions they may have about the patients’ participation in the study.

A personal consultee opinion form will be provided indicating that: the information given, orally and in writing, has been read and understood; the patients’ participation is voluntary and can be withdrawn at any time without consequence; and that, in the personal consultees’ opinion, the patient would not object to taking part in the trial.

After verifying that the personal consultee information sheet and opinion form are understood, the person seeking opinion will invite the personal consultee to sign the opinion form and will then add their own name and countersign it. A copy will be given to the personal consultee, a copy placed in the patient’s medical notes, and the original kept in the Investigator Site File.

If a personal consultee advises that, in their opinion, the patient would not choose to participate in the trial, then the trial treatment will be stopped (if ongoing) and the personal consultee asked whether, in their opinion, the patient would be willing to continue with ongoing data collection. Where a personal consultee is unable to visit the patient in hospital (e.g. due to infection control measures), this consultation may take place over the telephone. The consultation should be conducted by an experienced member of the site research team with knowledge of intensive care. The telephone consultation should be witnessed by another member of staff. The personal consultee information sheet may be sent to the personal consultee by email or by post. The outcome of the consultation will be documented and signed by the person seeking opinion on the personal consultee telephone opinion form, countersigned by the witness.

Upon patient recovery, the patient will be approached directly for informed deferred consent. The patient’s decision will be final and will supersede the personal consultee where there is disagreement.

